### Statistical analysis plan

The target sample size for the study is 1000 patients. The primary remit of TJBM study is to establish a central data repository that will support the development and delivery of precision medicine for all patients with glioma in the UK. As such, there is no statistical basis behind the choice of target sample size, but this number will allow robust assessment of feasibility and subgroup analyses. Sample size for any clinical trials that are subsequently linked to the platform will be based on statistical justification.

A formal interim analysis of the primary outcome measure (TTMD) and any relevant secondaries will be performed after registration and diagnosis of the first 100 patients and after 500 patients. There are no formal stopping rules. Formal analyses of all study outcome measures will be performed once the study has completed recruitment (target 1000 patients) and completed the follow-up for all registered patients.

The analysis of TTMD will essentially be descriptive. The median TTMD will be reported overall and for each centre, together with the proportion of patients achieving TTMD within 28 days. Graphs of the change in both these summary statistics over time will be used to explore if TTMD changes during the course of the study. All estimates will be accompanied by 95% CIs. The time to completion of each node of tissue and imaging pathway will be reported as medians together with 95% CI, both overall and for each centre. Swimmer plots will be used to depict overall and node level timings for each patient.

For each type of tumour and biological sample, the proportion of sample passing QC and successfully undergoing WGS and EC will be reported with 95% CI and similarly for the imaging QC outcome measures. Inter-rater agreement of RANO will be assessed through Kendall’s coefficient of concordance.

Extent of surgical resection is evaluated from the postoperative MRI scan and is categorised as either closed biopsy, open biopsy, debulking <50%, subtotal resection 50%–90%, near total resection 90% to <100% or gross total resection 100%. The extent of surgical resection will be reported as the proportion falling into each category together with 95% CI.

OS is defined as the time from date of diagnosis to the date of death with patients who are alive at the time of analysis censored at the date last seen in clinic. Intracranial PFS time is defined as the time from date of registration to the earliest of date of intracranial progressive disease or death from disease. The date of an event is defined as the earliest confirmation of progression by radiological assessment, clinical symptoms or multidisciplinary team (MDT). Patients without progression at the time of analysis will be censored at the date last seen in clinic.

OS and intracranial PFS will be analysed and plotted using the Kaplan-Meier method. Median times with corresponding 95% CI will be reported together with rates at 1, 2 and 5 years. Multivariable survival regression modelling will be used to explore prognostic factors, including, but not limited to, WHO 2021 classification, age, tumour volume, stage, methylation and mutation status.

Longitudinal measures of QoL will be generated from the QoL questionnaire according to the questionnaire-specific algorithms for scoring. The analysis of longitudinal QoL scores will essentially be descriptive. For each of the multiple QoL scores generated from the different questionnaires, the means, medians or proportions (as appropriate) will be plotted over time together with 95% CI. These repeated measures over time may be modelled, if appropriate, with a linear or more flexible mixed model that takes account of the within-subject correlation and will allow exploration of factors associated with the outcome.

Details of the type of intervention received and complications (eg, surgical wound infection) relating to SoC treatments received will be monitored and recorded throughout the follow-up period and reported descriptively as frequencies and associated percentages. In relation to initial local logical diagnosis, local pathological diagnosis and integrated histological–molecular diagnosis, any difference between the tiers of diagnoses will be highlighted and categorised as discordant, agreed, refined and reported descriptively as frequencies and associated percentages.

Confirmation of central storage of images and material, relevant targetable mutations identified by WGS and EC, and receipt of postmortem consent forms with confirmed central storage of samples will be recorded and reported descriptively.

Planned subgroup analyses of outcome measures include the following: IDH mutated and wild-type tumours; residual enhancing disease (none, operable, inoperable); methylated and unmethylated tumours; age groups; types of diagnosis (WHO 2021 criteria only, epigenetic classification only, WGS analysis only, integrated diagnosis comprising all three); performance status; sex; biomarkers that emerge during the study (either discovered in the TJBM study or reported in the literature) that are deemed relevant after review by the Scientific Advisory Board (SAB).

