### Platform study outcome measures

The primary outcome measure of the platform is time from biopsy to integrated histological–molecular diagnosis (TTMD) defined as the difference (in days) between date of biopsy and date of WGS and epigenomic classification (EC).

Secondary outcome measures include those that are process centred, patient centred and framework based.

Process-centred secondaries include time to completion of each node of tissue and imaging pathway, tumour and biological sample(s) quality control (QC) status, imaging QC status and inter-rater agreement of response assessment in neuro-oncology (RANO).^26^

Patient-centred secondaries include extent of surgical resection, overall survival time (OS), intracranial progression-free survival time (PFS), QoL scores, type of interventions received, type of complications from treatments (standard of care) received, and concordance between initial local radiological diagnosis, local pathological diagnosis and integrated histological–molecular diagnosis.

Research framework–based secondaries include samples and images centrally stored, targetable mutation(s) identified, postmortem sampling consent status and sample collection confirmation, and number of applications to, and outputs resulting from, data repository (including trial proposals both within and outside of the TJBM network).

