### Imaging data

Pseudo-anonymised longitudinal clinical imaging (MRI) for each patient will be collected and stored at a central imaging hub overseen by the Edinburgh Imaging Hub. Disease response assessment will be performed by practising UK neuroradiologists with a neuro-oncology interest via the Edinburgh Imaging Platform and additional analyses undertaken through the University of Edinburgh image analysis laboratory with permitted partners.

As per patient standard of care, it is expected that imaging will be performed preoperatively and postoperatively, for radiotherapy planning, following any chemoradiation, and as per follow-up determined by the managing MDT and/or if clinical concerns are raised regarding disease progression.

Pragmatic MRI protocols will be conducted as per SoC MRI protocols and timing following diagnosis and as such will be informed by the National Institute for health and Care Excellence guidelines from 2018,^30^ in line with the recent British Society of Neuroradiologists imaging guidance,^31^ which is itself an implementation of the Brain Tumour Imaging Protocol proposed by Ellingson.^32^ Where additional advanced imaging is performed, this is also encouraged to be submitted to the Edinburgh Imaging Hub and will be catalogued to permit any relevant subsequent analysis. Biopsy location imaging should also be submitted and standard operating protocols for the major neuro-navigation systems followed. Radiotherapy planning imaging will also be submitted.

The RANO assessments will be performed through a secure web portal provided by QMENTA Inc. There will be an ongoing 10% re-read to assess inter-rater agreement. It is anticipated that RANO reports will be provided within 2 weeks (10 working days) of successful transfer of imaging requiring assessment. RANO reports will categorise response where possible into complete response, partial response, stable disease or progressive disease. In cases of diagnostic uncertainty, potential or provisional outcomes may be recorded, allowing progression events to be backdated to the correct time point should subsequent imaging be confirmatory.

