All imaging will receive primary radiological reports at the local site as per current standard clinical practice. To deliver the imaging outcome requirements for clinical trials, centralised RANO reads will be delivered by a core group of UK Consultant neuroradiologists with a subspecialty interest in neuro-oncology imaging from TJBM study sites. Radiotherapy planning data in the form of dose distribution maps and associated data will be integrated into the imaging database to permit subsequent analysis of spatiotemporal response patterns of different glioma–treatment combinations in light of received radiation dose.

Local radiological reporting will inform clinical decision-making for individual patients. Central image analysis will provide resilient standardised assessment to meet internationally accepted standards which are suitable for peer-reviewed publication and are accepted by major regulatory approval bodies. All relevant preoperative and subsequent imaging will be identified for pseudonymisation and uploaded to the BRAIN MATRIX Imaging Platform in Edinburgh. This will be achieved through a dedicated online secure portal, with alternative secure online and physical transmission pathways available for redundancy. The accrued imaging data will form a core resource that will be leveraged for future imaging and clinical radiological research. The platform can also provide the basis for additional imaging studies within non-SoC imaging and advanced techniques, which would be separately funded and detailed in their respective project documentation.

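### Kendall's coefficient of concordance is the only statistic named for RANO inter-rater agreement, but it measures association of rankings and can substantially overstate agreement on the category

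*Protocol article*

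**What the plan says.** Under Platform study outcome measures, the process-centred secondary outcomes include "imaging QC status and inter-rater agreement of response assessment in neuro-oncology (RANO"). The Imaging data section sets the scale: "RANO reports will categorise response where possible into complete response, partial response, stable disease or progressive disease". The same section gives the source of the agreement data: "There will be an ongoing 10% re-read to assess inter-rater agreement". The Discussion (Justification for methodology) says who reads: "centralised RANO reads will be delivered by a core group of UK Consultant neuroradiologists".

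The Statistical analysis plan section then fixes the statistic: "Inter-rater agreement of RANO will be assessed through Kendall’s coefficient of concordance". The article names no kappa, percentage agreement or other measure of absolute agreement for RANO. It does not state how many reads a re-read scan receives, how readers are allocated, what mix of categories is expected, or any target value for W.

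**The concern.** The named outcome is agreement, and the four RANO categories have absolute meaning: progressive disease is an event and stable disease is not. W ranks the scans within each reader and compares the rankings. A reader who is consistently one category more severe than a colleague orders the scans in almost the same way, so W can stay high while the two often give different categories.

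The scale is a second difficulty. Kappa-type coefficients are 0 at chance, but W is not. A reader used to kappa could take a W of 0.5 for moderate agreement when, with two reads per scan, it is what unrelated reads produce.

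The third difficulty is conditional. W in its usual form needs every reader to rate every scan. If re-reads come from varying pairs within the reader group, it is not directly applicable.

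At stake is how far the platform's report on the reproducibility of its central reads can be trusted. The article offers those reads as a standardised assessment suitable for clinical trials.

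**Working it through.** The article gives no figure for this outcome, so there is nothing to reproduce. The check asks what W returns when the true level of agreement is known.

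**Inputs.** From the article: four ordered categories (CR, PR, SD, PD), a 10% re-read, and W as the statistic. Assumed: m = 2 reads per scan, n = 100 scans, and the category mixes shown below.

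**Formulas.** With tie correction, W = 12S / [m²(n³ − n) − mT]. S is the sum of squared deviations of the rank totals, and T is the sum of (t³ − t) over all tied groups of both readers. In terms of the mean pairwise rank correlation r, W = [1 + (m − 1)r]/m. This is exact without ties and nearly exact with them. Kappa = (observed − expected agreement)/(1 − expected agreement).

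**Step 1: chance value.** With r = 0, W = 1/m, which is 0.50, 0.33 and 0.20 for m = 2, 3 and 5. Simulation with independent readers gave 0.50, 0.34 and 0.20. For m = 2 and n = 100 the central 95% range was about 0.40 to 0.60, while kappa averaged about 0.

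**Step 2: systematic shifts.** For n = 100 and m = 2, m²(n³ − n) = 4 × 999,900 = 3,999,600.

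- *Mix 5/15/50/30, reader 2 one category worse, capped at PD.* S = 191,500 and T = 670,800. W = 2,298,000 / (3,999,600 − 1,341,600) = 0.86. Exact agreement is 30%.
- *Mix 5/15/50/30, reader 2 calls half of reader 1's SD scans PD.* S = 249,000 and T = 340,800. W = 2,988,000 / (3,999,600 − 681,600) = 0.90. Observed agreement is 0.75. Expected agreement is 0.05×0.05 + 0.15×0.15 + 0.50×0.25 + 0.30×0.55 = 0.315. Kappa = 0.435/0.685 = 0.635. Specific agreement for PD is 2×30/(30 + 55) = 0.71.
- *Mix 10/40/50/0, reader 2 one category worse.* S = 270,000 and T = 379,800. W = 3,240,000/3,240,000 = 1.00. Exact agreement is 0%.
- *Mix 5/15/40/40, reader 2 one category better, capped at CR.* S = 288,375 and T = 267,300. W = 3,460,500/3,465,000 = 0.999. Exact agreement is 5%.

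| Case | Exact agreement | W | Kappa | Linear-weighted | Quadratic-weighted |
|---|---|---|---|---|---|
| Full shift worse, 5/15/50/30 | 30% | 0.86 | −0.03 | 0.22 | 0.51 |
| Half of SD called PD, 5/15/50/30 | 75% | 0.90 | 0.635 | 0.73 | 0.84 |
| Full shift worse, 10/40/50/0 | 0% | 1.00 | −0.32 | 0.09 | 0.47 |
| Full shift better, 5/15/40/40 | 5% | 0.999 | −0.23 | 0.20 | 0.57 |

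**Step 3: does W respond to disagreement between SD and PD?** Assumed mix 2/5/53/40, with a growing share of reader 1's SD scans called PD by reader 2:

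| SD moved to PD | 10% | 20% | 40% | 100% |
|---|---|---|---|---|
| W | 0.96 | 0.92 | 0.86 | 0.70 |
| Kappa | 0.91 | 0.81 | 0.64 | 0.15 |

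W falls, but more slowly than kappa and towards a chance value of 0.5 instead of 0.

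**Step 4: tie correction.** Without it, which is not the usual choice for a four-category scale, W is lower: 0.57, 0.75, 0.81 and 0.87 for the four cases in Step 2, and 0.41 to 0.47 at chance.

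**The case against.** A reader might infer that W cannot show disagreement about progression, or that it would certify poor central reads as concordant. The article does not support either reading. Step 3 shows that W does fall when one reader over-calls progression, because PD is the end category and over-calling it creates ties. No threshold, target or decision is attached to W, so nothing is certified by it.

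The most striking figures are worst cases. W of about 1.00 needs a shift of one category on every scan and a favourable mix. The 0% agreement case also needs a first reader who records no progression, which is implausible in a study with intracranial PFS as an outcome. With mix 2/5/53/40, the same full shift towards worse categories gives W = 0.70.

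Two design points are not stated in the article: two reads per scan, and varying reader pairs. The 0.5 chance value and the objection about incomplete ratings depend on them.

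The consequence is also bounded. This is one of several process-centred secondary outcomes in a study without study treatments or formal stopping rules. Local reporting guides patient care, and PFS events may also be confirmed by clinical symptoms or the multidisciplinary team.

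All of this stands, and it limits the size of the point. It does not remove it. The outcome is called agreement and the only named statistic measures association of rankings. Because the article itself fixes that statistic, it is not a detail left to a separate analysis plan.

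**Conclusion.** The point holds in a bounded form. As the only measure of RANO agreement, W answers a different question from the one the outcome poses, and it can substantially overstate agreement when readers differ systematically. Realistic to severe examples give 0.90 against a kappa of about 0.63, and 0.86 with 30% exact agreement; values near 1.00 with 0% to 5% agreement are the extreme. All of these rest on assumed category mixes, two reads per scan and tie-corrected W. The chance value of about 1/m does not depend on the mix, but it does depend on the number of reads. Whether W can be applied at all to the re-read sample depends on a reader allocation that the article does not give. The effect is confined to one descriptive secondary outcome. It is worth correcting because the correction is cheap, and it does not threaten the primary outcome.

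**What to change.** Change the sentence in the Statistical analysis plan section so that the main measure is a chance-corrected agreement coefficient with its weights stated. Linear-weighted kappa would do for a fixed pair of readers; Krippendorff's ordinal alpha or Gwet's AC2 would suit varying pairs. Give a 95% CI that accounts for repeated scans from one patient, for example from a bootstrap that resamples patients.

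The weights need to be named because quadratic weights are also lenient: in the worked cases with 0% and 5% exact agreement they give 0.47 and 0.57, where linear weights give 0.09 and 0.20.

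Beside the coefficient, report exact percentage agreement, specific agreement for progressive versus not progressive disease, and the cross-table of reads. State the number of reads per re-read scan and how readers are allocated. W may stay as a supplement. These are per-scan measures and do not directly quantify disagreement on the date of progression.

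The cost is essentially one sentence. The same re-read data serve and no extra reads are needed.

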### Patient selection

Patients aged ≥16 years with newly diagnosed suspected WHO Grade II–IV glioma (as evidenced radiologically) suitable for a diagnostic or therapeutic surgical procedure resulting in a tumour sample matched to a blood sample or with progression with known WHO Grade II–IV glioma will be eligible.

Patients with primary spinal cord tumours, who are receiving active treatment of other malignancy, have contraindications to MRI and/or without standard of care imaging available, will be excluded.

Newly diagnosed patients with suspected WHO Grade II–IV glioma who are subsequently found to have a WHO Grade I tumour or non-brain tumour are expected to be a rare occurrence. If this event occurs:

If it is confirmed as a Grade I tumour, then the patient will remain eligible for the study and will continue to be followed up in accordance with the protocol.If it is confirmed as a non-brain tumour, then the patient will not remain on the study and no further follow-up data will be collected.

All patients must be able to provide written informed consent for the study.

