## Discussion

### Justification for patient population

The main aim of the TJBM study is to test the hypothesis that comprehensive genomic and epigenomic profiling of gliomas is feasible in a timely manner in the UK, and that the results improve stratification of patients for next-generation (targeted) therapies, ultimately improving outcomes and QoL.

Gliomas occur at all ages and their specific subtype is difficult to predict preoperatively. Therefore, the patient population eligible for the TJBM study is broad. It includes any patient who on preoperative assessment is suspected to have a diffuse glioma, or where a diffuse glioma remains a credible differential diagnosis, as established by the MDT at the recruiting site.

Recruitment is also open to patients with diffuse or atypical gliomas who had a biopsy before the launch of the TJBM study. This approach ensures that:

Patients with slow-growing diffuse gliomas that evolve over many years (oligodendrogliomas) may benefit from one or more of the clinical trials developed as part of the TJBM study and sample collection at tumour progression.Patients who potentially benefit most from comprehensive molecular diagnostics are not missed, which often are those with rare or atypical variants of glioma based on current diagnostics.^34^

The infrastructure for children with brain tumours in the UK is different to that of adults with epigenomic classification regularly used and with WGS shortly to be made available for all children with cancer. Thus, the challenges and opportunities are different for paediatric patients. Nevertheless, it is intended that children will be included within the TJBM study wherever appropriate. The recruitment of children and adolescents into the TJBM study will be coordinated with the UK’s paediatric oncology expert group(s).

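### OS is timed from an undefined date of diagnosis, although patients may enter at progression or after an earlier biopsy; without delayed entry, OS from original diagnosis is biased upward

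*Protocol article*

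**What the plan says.** The Statistical analysis plan section sets two time origins. For survival, "OS is defined as the time from date of diagnosis to the date of death". The censoring rule for OS has "patients who are alive at the time of analysis censored at the date last seen in clinic". For progression, "Intracranial PFS time is defined as the time from date of registration to the earliest of date of intracranial progressive disease or death from disease". Both use the same method: "OS and intracranial PFS will be analysed and plotted using the Kaplan-Meier method". The output is also fixed: "Median times with corresponding 95% CI will be reported together with rates at 1, 2 and 5 years". Exploratory multivariable survival regression is then to examine prognostic factors, with WHO 2021 classification and mutation status among those named.

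Entry is not limited to new cases. Patient selection admits newly diagnosed suspected glioma "or with progression with known WHO Grade II–IV glioma will be eligible". Justification for patient population adds: "Recruitment is also open to patients with diffuse or atypical gliomas who had a biopsy before the launch of the TJBM study". It gives slow-growing tumours that evolve over years as one reason. Sample collection provides for patients who have no new surgery and contribute tissue from a previous operation. Patient selection requires written consent from everyone.

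The article does not say which diagnosis date starts OS (original, local pathological or integrated). It mentions no entry time for the risk set. Newly versus previously diagnosed is not among the named subgroups.

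**The concern.** A patient who registers at progression, or on tissue from an old biopsy, was alive at registration by definition. Patients diagnosed at the same time who died sooner could never register. If the clock starts at original diagnosis and the late entrant counts as at risk from day zero, the interval from diagnosis to registration adds person-time in which no death could be observed. This is left truncation, and ignoring it raises the Kaplan-Meier curve.

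The planned OS median and landmark rates are at stake, as are the prognostic models. If carriers of some factor tend to enter late, they bring more guaranteed survival time and the factor can look protective when it has no effect. The article itself says that slow-growing gliomas are recruited this way, and tumour classification and mutation status are named covariates.

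PFS raises a different and smaller issue. It starts at registration, so it has no such guaranteed time. But for a newly diagnosed patient it measures time to first progression, and for a patient entering at progression it measures time to a later one. A combined PFS curve mixes the two.

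**Working it through.** The plan gives no OS figure to reproduce, and it states that the sample size of 1000 has no statistical basis. The check therefore asks how large the bias could be.

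**Inputs from the article.** Glioblastoma median survival is 12–14 months (Introduction); the midpoint, 13, is used.

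**Assumptions, not in the article.** Survival is exponential, entry time is independent of prognosis, a share p of enrolled patients enters late, and late entry falls between 6 and 24 months after diagnosis.

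**Formula.** S(t) = exp(−λt) with λ = ln 2 / 13 = 0.0533 per month, so S(12) = 0.527 and S(24) = 0.278. A late entrant who joins at time L has apparent survival 1 up to L and S(t)/S(L) afterwards. Hence

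S_naive(t) = (1 − p)·S(t) + p·E[min(1, S(t)/S(L))].

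**One case by hand** (p = 25%, all late entrants at L = 12 months). Beyond 12 months, S_naive(t) = S(t)·(0.75 + 0.25/0.527) = 1.224·S(t).
- Median: S(t) = 0.5/1.224 = 0.4085, so t = −ln(0.4085)/0.0533 = 16.8 months against 13.
- 2-year OS: 1.224 × 0.278 = 0.340 against 0.278.

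**Entry spread over 6–24 months.** The lower figure in each range weights entry times by survival; the upper takes them as uniform among those enrolled.

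| Late entrants | Naive median OS (true 13.0 months) |
|---|---|
| 2–5% | about 13.3–13.9 |
| 10% | 14.6–14.8 |
| 20% | 16.4–16.7 |
| 30% | 18.1–18.7 |
| 40% | 19.8–20.6 |

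At 20%, 1-year OS reads 61% against a true 53%.

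**Sensitivity to the lag.** With entry 0–6 months after diagnosis and 10–20% late entrants, the naive median is only about 13.3–13.7 months. With exponential lags (mean 6–24 months before selection on survival), it is 13.5–14.1 at 10%, 14.3–15.7 at 25% and 15.6–18.6 at 50%. A 10-year median, with 40% entering 1–10 years after diagnosis, gives 5-year OS of 80% against 71%.

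**Does delayed entry repair it?** In the simulations with a 13-month median and exponential lags, starting each patient's time at risk at registration while keeping the clock from diagnosis returned medians of 12.9–13.1 months and 2-year OS of 0.276–0.279 (true 0.278). This holds because entry was simulated as independent of prognosis.

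**Regression.** Two groups with identical hazards, differing only in their share of late entrants, were simulated. The naive Cox hazard ratio for a factor with no effect was about 0.86 (10% versus 30% late), 0.81 (10% versus 40%) and 0.70 (5% versus 50%). With delayed entry all three returned to 0.98–1.02.

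**The other meaning of diagnosis.** Suppose the date of a diagnosis made within the study is meant. The time before entry then drops out of OS. But OS would start after registration, while "Intracranial PFS time is defined as the time from date of registration". A patient who dies of disease without earlier progression would have PFS longer than OS, by the gap between registration and diagnosis. Deaths before the diagnostic report would have no valid OS time.

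**The case against.** The strongest reply is that diagnosis is a legitimate origin for OS and that Kaplan-Meier does not exclude delayed entry. Risk-set construction is often left to a separate analysis plan, which is not shown here. The article also speaks of an interim analysis after registration and diagnosis of the first 100 patients, which could mean a diagnosis made within the study. Part of this stands: the origin is not wrong in itself, and the bias depends on how the undefined date is read. But the article fixes origin and method while admitting patients for whom the two do not fit together, and the other reading brings its own defect.

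Several stronger readings are tempting but unsupported:
- A reader might infer that both entry types are pooled in every survival analysis. The article does not say so. It does not present its subgroup list as exhaustive, and its covariate list is explicitly open.
- A reader might add younger age to the factors that would look protective. The text links late entry only to slow-growing tumours and to rare or atypical variants.
- A reader might conclude that PFS is biased because its origin differs from that of OS. Different origins alone do not bias PFS.
- A reader might treat a large inflation as established. The article gives neither the share of late entrants nor their time since diagnosis, and small shares or short lags give little bias.
- A reader might hold that the entry types must never be combined. With delayed entry and stratification they can be, if entry is non-informative.

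**Conclusion.** The point holds in a limited form and should be fixed. Read with original diagnosis as the origin and everyone at risk from time zero, the stated rule biases OS upward, and the direction does not depend on the assumptions. The size does. Under the 13-month, 6–24-month scenario it runs from under one month on the median at 2–5% late entrants to between five and six months at 30%. Patients registered around first surgery are little affected. Read with an in-study diagnosis as the origin, the bias largely disappears, but OS and PFS no longer fit together. The definition needs repair on either reading.

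It is not a critical defect. OS is one of several secondary outcomes, its analysis is estimation and exploration, no stopping rule depends on it, and the primary outcome, time to integrated diagnosis, is untouched by this point.

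**What to change.** 1. State which diagnosis date starts OS.
2. For any OS from original diagnosis, use left-truncated risk sets with entry at registration. Alternatively, time OS from registration for patients who enter at progression or with earlier tissue.
3. Report OS and PFS separately for newly and previously diagnosed patients, and stratify the regression models by entry type.
4. State that delayed entry removes the bias only if entry time is independent of prognosis. That is doubtful for patients who enter because they have progressed, so their OS from original diagnosis needs this caveat.

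The cost is analysis wording and fewer patients behind each separate estimate. The diagnosis and registration dates are already needed for the stated endpoints, and entry type is known from eligibility, so no new data are needed.
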